### Study design

JAKPPPOT is an open-label, single-arm, mixed-methods feasibility trial, conducted at St John’s Institute of Dermatology, Guy’s and St Thomas’ NHS Foundation Trust, UK (figure 1). Participants (n=20) will receive 8 weeks of treatment with the JAK inhibitor upadacitinib (‘Rinvoq’, 30 mg, once-a-day). Integrated qualitative semistructured interviews (up to n=40) will be undertaken with trial participants, trial decliners and healthcare professionals. Recruitment optimisation strategies will be identified and implemented via the QRI process incorporated into this trial. The study endpoint is 20 participants successfully recruited, or 24 months elapsing, whichever occurs first.

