### Sample size rationale

We will aim to recruit 20 participants, in keeping with other published feasibility studies.^24 25^ Over a 24-month recruitment period, we anticipate approaching a total of around 100 potentially eligible individuals. Based on previous experience, we anticipate that the actual recruitment rate would be no less than 20%, so this would provide us with at least 20 participants.

With 100 approached participants, if 20 (20%) are recruited into the trial, this would allow us to estimate the 95% CI for the recruitment rate with precision of at least ±8%. Assuming 75% of participants adhere to treatment at least 80% of the time (as observed in APRICOT), a sample size of 20 participants would allow us to estimate ≥80% treatment adherence with a 95% CI: 51% to 91%. With 20 participants on treatment, JAKPPPOT will estimate a PPPASI50 in the JAK inhibitor arm with precision of at least ±3.43 PP-PASI points. This is based on figures derived from the APRICOT (mean baseline PP-PASI: 17.8; SD for the PP-PASI change at 8 weeks in active arm: 7.32).^16^ A PPPASI50 is an outcome that has been analysed as a primary/secondary endpoint in several PPP trials and was described as ‘treatment success’ during patient and public involvement (PPI) discussions with people with PPP.^26^ The PP-PASI reduction in the treatment arm will inform the sample size calculation for a larger definitive trial.

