### Progression criteria and rationale

Progression criteria have been outlined to determine whether it is appropriate to progress to a subsequent adequately powered RCT, shown in table 2. Findings from the primary and secondary quantitative outcomes will be incorporated with the qualitative findings to inform decisions regarding an ‘intermediate’ results in any domain (ie, upgrade to feasible or downgrade to non-feasible). All recommendations will be reviewed by the trial steering committee (TSC). For criteria judged to be intermediate or non-feasible, the study team will examine the likely causes and consider whether a mitigation strategy could be successfully implemented.

**Table 2 T2:** Progression criteria for the JAKPPPOT trial

Domain	Non-feasible	Intermediate	Feasible
Recruitment: proportion of potential participants identified who enrolled in the trial	<20%	20–40%	>40%
Adherence: proportion of participants achieving ‘Good’ adherence (>80% of medication taken as prescribed)	<20%	20–80%	>80%
Acceptability: proportion of participants who view JAK inhibitor therapy in PPP to be ‘acceptable’	<20%	20–80%	>80%

JAK, Janus kinase; JAKPPPOT, Janus kinase inhibitors in palmoplantar pustulosis: a mixed-methods feasibility; PPP, palmoplantar pustulosis.

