### Statistical analysis

Baseline characteristics will be summarised by using suitable measures of central tendencies. For continuous data, means/medians and SD/IQR will be reported depending on the data distribution, and frequencies with proportions will be reported for categorical data. The primary feasibility outcomes will be reported as proportions with a 95% CI. No formal hypothesis testing will be conducted as this is a feasibility study. A detailed statistical analysis plan has been written for the analysis approach.

The mean change in PP-PASI at week 8 for the treatment arm will be estimated with a 95% CI. This analysis will follow an intention-to-treat principle and include all participants with a non-missing outcome, regardless of how much treatment was received. Every effort will be made to reduce missing data. No imputation will be made for missing data for this feasibility study. Patterns of missingness will be explored and its relationship to the outcome described.

For the comparison with the historical control data, the analysis model will be a linear (Gaussian) mixed effect model, using PP-PASI scores from weeks 1/4/8, adjusted for baseline PP-PASI. This model will include a random effect for participant and fixed effects for time, time-by-treatment group interaction and baseline PP-PASI.

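### The ±8-point precision for the recruitment rate is right for 20 of 100 but is worded as a minimum, and stopping at the 20th participant makes it worse at higher rates

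*Protocol article*

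**What the plan says.** Five statements in the protocol article bear on this point.

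- **Sample size rationale, expected denominator:** "Over a 24-month recruitment period, we anticipate approaching a total of around 100 potentially eligible individuals".
- **Sample size rationale, expected rate:** "we anticipate that the actual recruitment rate would be no less than 20" per cent, from which the section concludes that 20 participants or more will be obtained.
- **Sample size rationale, precision:** the scenario is "With 100 approached participants, if 20 (20%) are recruited into the trial", and it is said to allow the team to "estimate the 95% CI for the recruitment rate with precision of at least ±8" per cent.
- **Study design:** "The study endpoint is 20 participants successfully recruited, or 24 months elapsing, whichever occurs first". The Primary outcomes section uses the same either/or rule for when the recruitment rate is assessed, and defines its denominator as everyone with direct contact with the research team.
- **Progression criteria, Table 2:** the domain "Recruitment: proportion of potential participants identified who enrolled in the trial" is graded non-feasible below 20%, intermediate from 20% to 40%, and feasible above 40%.

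**The concern.** The words *at least* present ±8 points as the worst precision to expect. The stopping rule caps the numerator at 20, so a denominator of 100 and a full complement of 20 recruits coincide at one rate only, 20%. The plan treats that rate as the bottom of its expected range. At any higher rate the 20th recruit should arrive before the 100th contact, and the rate is then estimated from fewer people than the precision statement assumes.

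The recruitment rate is a primary outcome and feeds a progression decision. A feasible grade reached through the 20-participant stop needs 49 or fewer contacts (20/49 = 40.8%; 20/50 is exactly 40% and does not exceed it). A reader who takes the planning statement at face value would expect a noticeably tighter interval there than the design can give.

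**Working it through.** **Inputs.** 20 recruits, about 100 approached, 20% as the lowest expected rate and 95% confidence (Sample size rationale; Statistical analysis). Stop at 20 recruits or 24 months (Study design; Primary outcomes). Thresholds of 20% and 40% (Table 2). A rate of 17% in the earlier trial (Recruitment).

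**Step 1: reproduce the plan's figure.** The normal-approximation half-width is 1.96 × √(p(1−p)/n). With p = 0.20 and n = 100 it is 1.96 × √(0.16/100) = 0.0784, or ±7.8 points. This rounds to the stated ±8.

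**Step 2: apply the stop at 20.** If recruitment ends at the 20th participant, n ≈ 20/p. Substituting gives a half-width of 1.96 × p × √((1−p)/20). For example, at p = 0.40 it is 1.96 × 0.40 × √(0.60/20) = 0.1358.

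**Step 3: separate the two causes of widening.** The last column holds n at 100, so it shows the effect of p(1−p) alone.

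| Rate | n at the stop | Half-width at the stop | Half-width if n were 100 |
|---|---|---|---|
| 20% | 100 | ±7.8 | ±7.8 |
| 25% | 80 | ±9.5 | ±8.5 |
| 30% | 67 | ±11.0 | ±9.0 |
| 40% | 50 | ±13.6 | ±9.6 |

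At 40% the total widening is 13.6 − 7.8 = 5.8 points. Of this, 9.6 − 7.8 = 1.8 comes from the higher proportion and 13.6 − 9.6 = 4.0 from the smaller denominator. The interval at 20/50 is 40% ± 13.6, or 26.4% to 53.6%.

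**Step 4: where the statement ceases to hold.** The half-width passes 8.0 points at a rate of about 20.5% (20/98 gives ±7.98; 20/97 gives ±8.05) and no longer rounds to 8 from about 22%. It falls below 8 again only above about 96%, which is not a realistic rate.

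**Step 5: below 20%.** Here the 24-month limit is expected to apply and n stays near 100. At 17% the half-width is 1.96 × √(0.17 × 0.83/100) = 0.0736, or ±7.4.

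**Step 6: how often the 20-participant stop comes first.** Treating contacts as independent, the probability of 20 recruits among the first 99 contacts is 23% at a true rate of 17%, 52% at 20%, 89% at 25% and 99% at 30%.

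**Step 7: people in contact but not yet enrolled at closure.** They add to the denominator, so n ≈ 20/p is approximate, and the documents give no figure for them. As an assumed range, suppose the 20th recruit comes at contact 50. With 0, 10 or 17 further people in contact, the result is 20/50 (±13.6), 20/60 (±11.9) or 20/67 (±11.0). It would take 48 more (20/98) to return to ±8.

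**The case against.** The strongest defence is that the precision statement is conditional. It names 100 approached and 20 recruited, and for that case it is correct. A reader might infer a calculation error, and there is none. A reader might also infer that the sections fix the denominator in two incompatible ways. They do not: the text says around 100 are anticipated, and 20 of 100 is the very point where the cap and the expected number of contacts agree.

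The Recruitment section also assumes a low rate, in line with the 17% of the earlier trial. At that rate ±8 holds and the 24-month limit usually comes first. Even at a true 20%, which stop comes first is close to a coin toss. This stands, and it limits the point to rates above 20%. It does not remove the point, because the sample size rests on 20% as the lowest rate expected and the plan intends to raise recruitment during the trial.

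It is also fair that no single planning precision applies at every proportion. Part of the widening would occur with n fixed at 100, so blaming the stopping rule for all of it would be wrong. At 40% it accounts for the larger part.

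A reader might infer that the progression decision will be made on a misleading interval. The Statistical analysis section rules that out: "The primary feasibility outcomes will be reported as proportions with a 95% CI", so the steering committee will see the interval for the denominator actually observed.

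Finally, a reader might object that the interval method for recruitment differs from that used for adherence. This is a preference that an analysis plan can settle. For 20/100 the average half-width is 7.8 by Wilson and 8.3 by Clopper–Pearson, and both round to 8.

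**Conclusion.** The point holds as a low-severity restatement of a planning figure. ±8 points is correct for 20 of 100. It is not a minimum over the anticipated range of 20% and above, where it is close to the best case: about ±9.5 at 25%, ±11.0 at 30% and ±13.6 at the 40% threshold.

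These sizes assume that recruitment ends at the 20th participant, that n is about 20 divided by the rate, and that a fixed-n binomial interval is adequate although stopping at a set number of recruits is inverse sampling. People still in contact at closure would enlarge the denominator and soften the figures somewhat. Changes to recruitment strategy during the trial make the independence behind the stopping probabilities approximate. Neither restores ±8 at 30% to 40% unless the number still in contact is large. Nothing here affects trial conduct or the interval that will be reported.

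**What to change.** In the Sample size rationale:

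1. Replace the *at least* wording with: *about ±8 percentage points if 20 of 100 are recruited*.
2. Add the expected precision at higher rates under the 20-participant stop: about ±9.5 points at 25% (n=80), ±11 at 30% (n=67), and ±14 at the 40% threshold (n=50, roughly 26% to 54%).
3. State that the denominator is the number of potential participants identified when recruitment stops, so it may be below 100, and that people in contact but not yet enrolled at that time are counted in it.

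The cost is a few sentences and a less favourable precision statement. No extra participants are needed, and neither the design nor the analysis changes.

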### Comparator

Retrospective placebo-controlled data from the APRICOT (National Institute of Health and Social Care Research [NIHR]reference: 13/50/17; Research Ethics Committee [REC] number: 16/LO/0436; International Standard Registered Clinical/soCial sTudy Number [ISRCTN] number: ISCRTN13127147) will be used to generate an indication of effect size for the purpose of estimating the required sample size of a definitive RCT.^16^ Placebo controls in the APRICOT previously received 0.67 mL of vehicle solution daily through self-administered subcutaneous injection over 8 weeks. The IMP in APRICOT was anakinra (Kineret; SOBI, Stockholm, Sweden; 100 mg/0.67 mL daily delivered via self-administered subcutaneous injection).

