#### Exploratory outcomes

The following outcomes are assessed after 24 months of recruitment, or when the recruitment target of 20 participants is achieved (whichever occurs first):

Evaluation of trial recruitment diversity and inclusion.Participant demographics will include age, sex, ethnicity and socioeconomic background.Accuracy of disease severity assessments of photographs compared to in-person assessments.PP-PASI and Palmoplantar Pustulosis-Investigator Global Assessment (PPP-IGA) grading of photographs will be compared with in-person disease severity assessments.Overall mean change in total pustule count over the 8-week treatment period, compared to baseline adjusted for baseline total pustule count.Placebo control data from the APRICOT (2015–2020, n=31 with complete data) will be used as a comparator.Overall mean change in fresh pustule count over the 8-week treatment period, compared to baseline adjusted for baseline fresh pustule count.Placebo control data from the APRICOT (2015–2020, n=31 with complete data) will be used as a comparator.Overall proportion of participants achieving clearance of PPP over the 8-week treatment period.Clearance will be defined as a PPP-IGA of 0/1.Placebo control data from the APRICOT (2015–2020, n=31 with complete data) will be used as a comparator.Overall mean change in chronic plaque psoriasis severity (if applicable) over the 8-week treatment period, adjusted for baseline chronic plaque psoriasis severity.Severity will be assessed using the PASI.^23^Placebo control data from the APRICOT (2015–2020, n=16 with complete data) will be used as a comparator.Overall mean change in participants’ symptoms and quality of life over the 8-week treatment period, adjusted for baseline. Dermatology Life Quality Index, Patient Global Assessment and European Quality of Life 5 Dimensions 5 Level Version (EQ5D-5L) will be used to assess participants’ symptoms and quality of lifePlacebo control data from the APRICOT (2015–2020, n=31 with complete data) will be used as a comparator.Overall proportion of participants achieving a 50% reduction in PP-PASI score (PPPASI50) over the 8-week treatment period, compared to baseline (visit 1).Placebo control data from the APRICOT (2015–2020, n=31 with complete data) will be used as a comparator.

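### The ±3.43 PP-PASI points given as the precision of PPPASI50 is the half-width for the single-arm mean PP-PASI change; PPPASI50 is a proportion and needs a precision in percentage points

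*Protocol article*

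**What the plan says.** Under Sample size rationale, the protocol article sets the target ("We will aim to recruit 20 participants, in keeping with other published feasibility studies") and then gives the precision expected from that number for several quantities. For efficacy it states that "JAKPPPOT will estimate a PPPASI50 in the JAK inhibitor arm with precision of at least ±3.43 PP-PASI points". The inputs, taken from APRICOT, are "mean baseline PP-PASI: 17.8" and "SD for the PP-PASI change at 8 weeks in active arm: 7.32". The section closes with "The PP-PASI reduction in the treatment arm will inform the sample size calculation for a larger definitive trial".

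Other sections bear on this statement:

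- Exploratory outcomes defines PPPASI50 as "Overall proportion of participants achieving a 50% reduction in PP-PASI score (PPPASI50) over the 8-week treatment period".
- Secondary outcomes lists the mean change in PP-PASI over 8 weeks, adjusted for baseline, with 31 APRICOT placebo participants as comparator.
- Statistical analysis says "The mean change in PP-PASI at week 8 for the treatment arm will be estimated with a 95% CI". It limits that analysis to participants with a non-missing outcome, rules out imputation, and plans a baseline-adjusted mixed model for the historic comparison.
- Comparator says the APRICOT placebo data will provide an "indication of effect size for the purpose of estimating the required sample size of a definitive RCT". The abstract also names those data as the effect size comparator.

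**The concern.** A responder outcome is a yes/no result for each participant. Its summary is a percentage, and the uncertainty of that percentage is in percentage points. A precision in PP-PASI points belongs to a mean score or a mean change. As written, the sentence pairs a binary endpoint with the precision of a continuous one.

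The same section describes PPPASI50 as an endpoint used in other PPP trials and as what patients regarded as treatment success. A reader could conclude that the treatment success rate will be well estimated, when 20 participants leave it very uncertain. This is also the only efficacy precision in the article, and informing the size of a later RCT is a stated secondary objective.

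A smaller, related point concerns the closing sentence of the section. It names the treatment-arm reduction as what will inform the RCT sample size, while the comparator section names an effect size against placebo. A within-arm reduction also contains whatever change would have occurred on placebo.

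**Working it through.** **Inputs from the protocol article**

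- n = 20 and SD of the 8-week PP-PASI change = 7.32 (Sample size rationale)
- Mean baseline PP-PASI = 17.8 (Sample size rationale)
- Historic controls: 31 with complete data (Secondary outcomes)
- 95% confidence level (Statistical analysis), taken as two-sided

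The article does not give the placebo SD, the correlation between baseline PP-PASI and change, or the expected PPPASI50 rate. These are treated as assumptions below.

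**1. Reproduce the stated figure.** For one mean with a t interval, half-width = t(0.975, n−1) × SD/√n.

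- t version: 2.093 × 7.32/√20 = 2.093 × 1.637 = 3.43, which matches.
- Normal version: 1.960 × 1.637 = 3.21, which does not match.

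So ±3.43 is the t-based half-width for a single-arm mean change.

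**2. Dependence on the number analysed.** Without imputation, n is the number with a week-8 score.

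| Analysed | Half-width (points) |
|---|---|
| 20 | ±3.43 |
| 18 | 2.110 × 7.32/√18 = ±3.64 |
| 16 | 2.131 × 7.32/√16 = ±3.90 |

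**3. Precision of PPPASI50 as defined.** The Wald half-width is 1.96 × √(p(1−p)/20). The exact interval is Clopper-Pearson.

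| Responders | Wald half-width (percentage points) | Exact 95% CI |
|---|---|---|
| 4/20 | ±18 | 6% to 44% |
| 8/20 | ±21 | 19% to 64% |
| 10/20 | ±22 | 27% to 73% |
| 15/20 | ±19 | 51% to 91% |

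The last row equals the interval that the same section gives for 75% adherence in 20 participants. The article therefore already handles one proportion at this sample size correctly.

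**4. Difference from historic placebo, for orientation only.** Assume SD 7.32 in both groups.

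- SE = 7.32 × √(1/20 + 1/31) = 2.10.
- With one baseline covariate, half-width = t(0.975, 48) × 2.10 × √(1 − r²), where t = 2.011 and r is the assumed correlation between baseline and change.
- r = 0 gives ±4.2; r = 0.3 gives ±4.0; r = 0.5 gives ±3.7; r = 0.7 gives ±3.0.

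This is a simple approximation to the planned mixed model. At r of about 0.6 the half-width would be close to 3.43, but only by coincidence, because the stated figure was not derived for a difference.

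**The case against.** The strongest reply is that this is a slip of wording. The calculation is correct, the sentence gives its units, and the next sentence gives its inputs, so an attentive reader can see that a mean change is meant. The authors may have had in mind a mean fall of half the baseline, 17.8/2 = 8.9 points, plus or minus 3.43. The planned analysis of mean change with a 95% CI is correctly specified, and PPPASI50 is only exploratory.

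Most of this stands, and it limits the weight of the point. It does not make the sentence correct: a mean fall of 50% is not the proportion of participants who achieve a 50% fall, which is how the article itself defines PPPASI50.

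Three stronger readings are tempting, and the document does not support them.

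- A reader might infer that the trial plans to size the RCT on the within-arm reduction alone, and so would under-size it. The text says only that this reduction will inform the calculation. The abstract and the comparator section take the effect size against APRICOT placebo. The closing sentence is loose, but it is not a plan to ignore the comparator.
- A reader might infer that no precision for the historic comparison has been worked out. The article is silent, but the full protocol and the analysis plan are not shown and may give it.
- A reader might take ±4.2 points as the true precision of that comparison. It rests on an assumed placebo SD and no gain from baseline adjustment, although that adjustment is prespecified.

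**Conclusion.** The point holds as an error in a stated figure. The ±3.43 PP-PASI points is the precision of the mean PP-PASI change at week 8 in the treatment arm, and only if all 20 participants are analysed and the SD of change is 7.32. It is not a precision for PPPASI50, which 20 participants estimate to about ±18 to ±22 percentage points over response rates of 20% to 75%.

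The closing sentence on the RCT sample size should be brought into line with the rest of the article, as a matter of clarity.

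The weight is minor to moderate. The target of 20 rests on other feasibility studies and expected recruitment. The primary outcomes are recruitment, adherence and acceptability. The progression criteria use neither PP-PASI nor PPPASI50, and no hypothesis is tested. No planned analysis changes.

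**What to change.** In Sample size rationale, replace the PPPASI50 precision statement with two separate ones:

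- Mean PP-PASI change at week 8: ±3.43 points with 20 participants analysed (±3.64 with 18).
- PPPASI50: about ±18 to ±22 percentage points; for example, 10 responders of 20 give an exact 95% CI of 27% to 73%.

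Reword the closing sentence so that the RCT sample size is informed by the baseline-adjusted difference from APRICOT placebo with its confidence interval, together with the SD, and not by the treatment-arm reduction alone.

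If a precision for that difference is quoted, give it as a range with its assumptions: about ±3.0 to ±4.2 points for a common SD of 7.32 and a correlation between baseline and change from 0.7 down to 0. Use the actual APRICOT placebo SD and correlation if they are to hand, since the team has patient-level data.

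The cost is two or three sentences. Design, data collection and analyses stay as they are; the stated precision for treatment success becomes visibly less favourable.
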